#### Outcome data collection

Assessment of participants is conducted through completion of online questionnaires for demographic data and outcome measures at baseline (T1=week 0); at end of intervention (T2=week 10) and at 10-week follow-up (T3=week 20). Such data is collected directly from the participants via online survey tool inbuilt within the trial.

#### Outcome measures

Sibling-participants will be assessed on the primary outcome and three further secondary outcomes at three time-points. Data collection using the following outcome measures tools is through online completion by all participants across the treatment and control conditions.

The primary outcome of this intervention is siblings’ mental wellbeing measured by a self-administered tool, the Warwick-Edinburgh Mental Wellbeing Scale (WEMWBS) [28]. WEMWBS has been validated to assess the impact of interventions on the mental wellbeing of a population sample [28]. Its brevity of 14 positively-worded items and 5 response categories make it ideal for use in this trial.

There are three secondary outcome measures, including: knowledge of mental health using Mental Health Knowledge Schedule (MAKS) [29]; self efficacy using the Assessment of Perceived General Self-Efficacy (APGSE) [30], and negative and positive experience of caring using Experience of Caregiving Index (ECI) [31].

The intervention, especially its psychoeducation component, is expected to impact on participants’ knowledge about psychosis. The MAKS is an ideal tool to assess and track stigma-related mental health knowledge amongst the sibling-participants. It has been validated for use in both face to face interviews and for online data collection [29]. To assess participants’ perceived self-efficacy with regard to optimistic beliefs about coping with a large variety of stressors, regardless of their circumstances, the online version of the APGSE [30] is used. This version, with a 10-item scale, has been found to be valid and feasible for online use. Finally, for assessing the sibling-participants’ experiences of caregiving, the ECI [31] will gather relevant information from siblings. The ECI contains 66 items covering 10 sub-scales of both positive and negative experiences of caregiving. In this trial, all 10 sub-scales inclusive of further break-down questions will be presented in a format of brief statements to the participants via an online questionnaire. The 10 sub-scales are: effects on family; stigma; negative symptoms; difficult behaviour; dependency; loss; positive personal experiences; and good aspects of the relationship with the service users; problems with services; and need for back up.

#### Process evaluation

Data on patterns of uptake and usage (number of hits, time spent on-line etc.) from all participants will be monitored to correlate efficacy with usage and to ascertain feasibility.

After completion of the follow-up questionnaire data (T3=week 20), about 20% of the participants (n=20) across the three treatment groups will be purposively selected for interview to explore their experiences of using the resource and the perceived acceptability of the intervention. Purposive selection is used to identify the participants to ensure representation of diverse experiences and views from those with ethnic minority backgrounds, frequent and infrequent users whose experiences may impact on their usage and outcomes. Conventional delivery of psychosocial interventions (i.e. face to face) is known to be less likely to be offered to or accessed by people with Black and Minority Ethnic backgrounds (BME) [7]. The purposive sampling for the process evaluation aims to investigate if the online delivery and medium addresses this well-known access and equality issue, in addition to seek to understand their experience and perceived acceptability of the intervention. A post-intervention individual semi-structured interview will be conducted in person, via phone or online conference, depending on the participants’ preference. In addition, data on patterns of uptake and usage from all participants, e.g. number of hits and time spent on the treatment condition allocated will be monitored to correlate effectiveness with usage and to ascertain feasibility.

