### Design

#### Randomisation, treatment allocation and blinding

This is a factorial design RCT in which participants are randomised and allocated to 4 conditions: 3 treatment conditions in addition to treatment as usual (control). The three treatment arms will allocate participants into either: psychoeducation alone; peer support alone; or combined psychoeducation and peer support. Screening for eligible participants against inclusion and exclusion criteria is conducted online through screening questionnaires. All eligible participants will then be allocated to one of the three treatment or the control condition. Randomisation is done using computer-generated permuted blocks and is carried out by an independent Clinical Trial Unit (CTU) to ensure blindness. Eligible participants will receive a computer-generated account with username and a unique password as well as the treatment group they have been allocated to.

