#### Inclusion criteria

This trial targets siblings of individuals diagnosed with FEP directly. Hence, 144 siblings will be recruited who fulfill the following inclusion criteria:

&z.squf; aged 16 or above;

&z.squf; has a brother or sister receiving service from a local EIPS at the time of joining the trial;

&z.squf; is based within the Greater London or Berkshire area themselves;

&z.squf; has had contact at least weekly with their ill brother or sister on average over the previous 3 months.

&z.squf; can read and understand English language in usual online communications.

&z.squf; has daily access to internet use.

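### The process-evaluation interviews can describe access barriers felt by enrolled minority siblings, but cannot show whether online delivery makes access more equal

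*Protocol article*

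**What the plan says.** All references are to the protocol article.

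The Process evaluation section states the problem first: conventional face-to-face delivery "is known to be less likely to be offered to or accessed by people with Black and Minority Ethnic backgrounds (BME". It then assigns the question to a sample: "The purposive sampling for the process evaluation aims to investigate if the online delivery and medium addresses this well-known access and equality issue". The same sentence adds experience and perceived acceptability as a further purpose.

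The sample is fixed in the same section: "about 20% of the participants (n=20) across the three treatment groups will be purposively selected for interview". The timing is "After completion of the follow-up questionnaire data (T3=week 20". The method is described as "Purposive selection is used to identify the participants to ensure representation of diverse experiences and views from those with ethnic minority backgrounds", together with frequent and infrequent users.

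The route into that sample is set elsewhere. Under Recruitment & Informed consent, siblings are identified through clinicians or refer themselves, and then consent. Under Randomisation, treatment allocation and blinding, "Screening for eligible participants against inclusion and exclusion criteria is conducted online through screening questionnaires", and eligible people then receive an account. The Inclusion criteria require that a sibling "can read and understand English language in usual online communications" and "has daily access to internet use".

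Demographic data (Outcome data collection) and usage data (Process evaluation) come from trial participants. The stated uses of the usage data are correlation with effect and assessment of feasibility. No comparison by ethnicity is described.

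**The concern.** Being offered an intervention and gaining access to it both come before enrolment. The question whether a new medium eases that problem is given to people who have all passed that point. Siblings who were never approached, who declined or who were screened out are not in the interview sample.

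The selection method removes a second possible signal. Because interviewees are chosen partly to ensure minority representation, their ethnic mix reflects the researchers' choice and not who was reached.

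At stake is what the pilot passes on to the definitive trial. The Background and Discussion sections argue for online delivery partly because it may reach siblings whom existing services miss. Favourable interviews with enrolled minority siblings could be carried forward as support for more equal access, which they cannot give. The English and daily-internet criteria might themselves filter some minority siblings out, and these interviews would not reveal it.

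**Working it through.** **1. The plan's own figure.** Sample size gives 36 recruited and 30 retained per arm.

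- Three treatment arms: 3 × 36 = 108 recruited, 3 × 30 = 90 retained. Then 0.20 × 108 = 21.6 and 0.20 × 90 = 18.0. Conversely, 20/108 = 18.5% and 20/90 = 22.2%.
- All four arms: 0.20 × 144 = 28.8 and 0.20 × 120 = 24.0.

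So n=20 fits about 20% of the three treatment arms, as stated. The figure is sound; the issue is what it is used for.

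**2. Question and sample side by side.**

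| Element | What the article fixes |
|---|---|
| Problem | Lower chance of being offered or reaching help |
| Stage concerned | Before enrolment |
| People asked | Enrolled, allocated to a treatment arm, account issued |
| When | After the week-20 questionnaire |
| Ethnic mix | Set by purposive selection |
| Comparator for medium | None: the control condition is also online, on the same trial website |

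Access takes the same value for every interviewee, so no access rate by ethnicity can be formed from them.

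**3. Illustration that the interviews cannot separate the cases.** Inputs from the article: five Trusts with 400 to 600 service users each, so 2000 to 3000 in total; 144 recruited; three of four arms interviewed. Assumptions, not in the article: caseload of 2000, one eligible sibling per service user, 30% minority share (600 minority, 1400 other), and minority participants spread evenly over the arms.

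| Enrolment rate, minority vs other | Ratio | Minority enrolled | Other enrolled | Minority in three treatment arms (× 3/4) |
|---|---|---|---|---|
| 7.2% vs 7.2% | 1.0 | 600 × 0.072 = 43.2 | 1400 × 0.072 = 100.8 | 32.4 |
| 3.6% vs 8.74% | 0.41 | 21.6 | 122.4 | 16.2 |
| 2.0% vs 9.43% | 0.21 | 12.0 | 132.0 | 9.0 |

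Each row gives about 144 enrolled. Suppose the interviews include 6 minority siblings out of 20 (0.30 × 20). Even the last row can supply them after the plan's 20% attrition: 9.0 × 0.8 = 7.2. The interviewed group would have the same composition under equal access and under a nearly five-fold gap (1/0.21 = 4.8).

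**4. What data on everyone enrolled could add.** The 95% half-width for a share p of 144 is 1.96 × √(p(1 − p)/144). At assumed p = 0.30 it is 0.075; at p = 0.50 it is 0.082. This is the precision of the enrolled minority share only. It is not the precision of an access gap, because the article gives no reference share to set it against.

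**The case against.** The strongest reply is that one sentence is being read too literally. Access by ethnicity is not among the trial objectives under Aims of the project. The Abstract gives the interviews' purpose as experience and acceptability, and mentions feedback on barriers. To investigate can mean to explore qualitatively: minority siblings, including infrequent users, can be asked whether face-to-face help was ever offered to them and what the online medium changed. Nothing in the article says that the interview mix will be read as an access rate. All of this stands, and it keeps the point small.

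It is also fair that the screening items and the participant-flow figure are not shown, so ethnicity may already be recorded at screening. Its absence from the article is no fault. Self-referral also matters: not every participant came through a clinician's offer, although every participant did gain access.

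A reader might go further and infer that the trial can say nothing about access. That is not supported. Online screening, participant demographics and usage logs could give a descriptive picture, provided ethnicity is recorded at screening. Nor do the documents show that the English and internet criteria create an ethnic gap. That is only a possibility, and the section on exclusion criteria explains the language and computer-skill requirements by what is needed to use the resource.

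What the reply does not remove is the assignment itself. The article names the access and equality issue and hands it to this sample. That is a mismatch of aim and sample, not a detail left to a fuller document.

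**Conclusion.** The point holds in a limited form. The interviews can describe experience, acceptability and perceived barriers among enrolled minority siblings. They cannot show whether online delivery has made offer or access more equal, because all interviewees gained access and their ethnic mix is chosen.

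This conclusion follows from the design and needs no assumed figure. The illustration of equal access against a nearly five-fold gap does rest on assumptions: the 30% minority share, the caseload of 2000 and one eligible sibling per service user.

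Severity is low. The point is secondary and affects neither the primary outcome nor the sample size. A reader might also infer that comparing the enrolled share with the Trusts' caseloads would settle the matter. It would not: the caseload describes service users and not siblings, recruitment also runs through carers' networks and self-referral, and there is no face-to-face comparator.

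**What to change.** 1. Restate the interview aim as exploring experience, acceptability and perceived access barriers among enrolled minority ethnic siblings, and drop the implication that the interviews test whether the access issue is addressed.
2. Base any descriptive statement on access on the recruitment flow. Tabulate ethnicity at screened, excluded (English and internet criteria shown separately), enrolled, ever logged in and week-20 questionnaire completed, split by clinician-identified and self-referred.
3. State the table's limit: it starts at screening, so people never approached stay unseen. Because screening is online, some people without ready internet access may never reach it.
4. Optionally, set the Trust-referred participants beside the aggregate ethnic mix of the EIPS caseloads. Label this a rough proxy and make no claim that online delivery closed a gap.

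The cost is a reworded sentence, one extra table and, only if ethnicity is not already asked, one item in the existing online screen. The optional comparison needs one aggregate figure per Trust.

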### The intervention

#### Development and building the intervention

The development of the online multi-component psychoeducational intervention is informed by the previous stages of the overall project, i.e. the theoretical development phase in the first 18 months. The theoretical phase of the overall study comprises two stages, including a mixed-method systematic review and a focus group study with siblings (See Figure 1).

The systematic review conducted in Phase I, and recently completed, has identified the evidence base of psychoeducational interventions for families and relatives of people with psychosis and the common essential ingredients, implementation factors (both facilitators and barriers) in those effective interventions [32]. The review, also informs the theoretical modelling of the related concepts and essential ingredients of the intervention to better understand how each ingredient works independently as well as interdependently to produce the desired primary and secondary outcomes in the target population. We have also reviewed outcome measurement tools used by previous studies and modified them as needed to suit the sibling-participants and the online medium of data-collection.

The theoretical understanding accomplished was further built on in a participative exploratory study involving siblings of individuals affected by psychosis. Focus group methodology was chosen because we were interested in understanding a range of perspectives and valued the insights gained through group discussion between siblings [33]. The views of siblings were as crucial as the evidence base drawn from the systematic review to ensure that the intervention addresses siblings’ specific needs in a contemporary context [34]. During the focus group discussions involving 14 siblings conducted in mid 2012, they were asked to help design the intervention in a way that would optimise utilisation, access and relevance of the intervention to their own needs and life-styles. They were also asked about what services they would like and in what medium and content they would like these services to be covered. Potential barriers were identified and strategies to overcome them developed [35].

The intervention is currently being built and engineered through intensive input of an Expert Advisory Group (EAG) and e-learning expertise, across the theoretical development and modelling phases in the MRC framework (see Figure 1). The EAG will comprise siblings (50%), service users, parents, mental health clinicians, youth organisation/ charity personnel and e-learning IT experts. Guided by the conceptual framework and design-content produced through the previous stages discussed above, the EAG will advise on the design and content of the psychoeducational intervention resource package built through a process of consultation forums, including: design and selection of the scripts / content for the information section, provision of textual/ audio-visual inputs and blog-building for the peer support section. It will also validate and review the online intervention being built, along the process. The process of these 2 parallel stages will follow the development cycle published recently by National Institute for Health Research Service Delivery and Organisation (NIHR) programme [36], reporting their successful experience of developing an online training resource. There will be five build steps in the development cycle: 1. draft architecture and content; 2. mock up of shell; 3. fill shell with material; 4.cross inference and integrate materials, and 5. prepare for piloting.

Finally, a usability evaluation (see Figure 1) will test the usability of the online intervention with 20 siblings, prior to the trial. The usability test will adapt Poulson et al’s framework [37] to collate data on ease of use, accessibility, logistic of navigation, and trial use of pre- and post outcome measures within the intervention. Both objective observation and subjective feedback from the usability evaluation users will be analysed and used to refine the intervention, ready for the exploratory trial.

#### Design and content of the intervention

It is anticipated that the final intervention will comprise multiple components and the following characteristics: psychoeducation focusing on information-giving on psychosis, common treatment and management strategies for symptoms; and a peer support element that uses a virtual discussion network with secured and moderated discussion boards on commonly encountered issues and experiences to facilitate mutual sharing and discussion between siblings. There are also supplementary links to relevant resources inbuilt within the psychoeducation and peer support components.

Within the two major components (i.e. psychoeducation and peer support) a modular approach will be used to incorporate both information-giving and active strategies that link learning/ knowledge to everyday life practice, as informed by the identified essential ingredients of effective interventions [32,38]. Most of these strategies could be described as cognitive-behavioural orientated and involve online and off-line practice/ homework tasks. The modular information-giving covers topics identified by siblings themselves in addition to the evidence-base as identified by the systematic review. These include, for example: causes of psychosis; common treatments; how could I help as a brother or sister?; looking after myself; what does the future hold? In addition to the textual medium as a major way of information giving, audio and video links will be used. Online discussion forums resembling a virtual support group for siblings, where they can discuss shared issues and exchange views with one another, is another important feature of the intervention. Considerations of confidentiality and anonymity, group safety and cohesiveness, are addressed in the design and delivery of the intervention, with additional IT-related issues. For instance, the online peer support is a closed virtual group limited to participants, all participants will use a username on the online discussion forum without any further information linked to themselves or their families. There will be professional-led facilitation/ moderation and regular monitoring across the online resource. A conceptual framework of the intervention design is illustrated in Figure 3.

**Figure 3 F3:**
[figure not shown]
Conceptual framework of the online intervention for siblings.

The intervention is designed for siblings’ use at their own home or base. They can access and use the intervention 24/7. Through online IT or phone helpdesk, support is provided depending on the participants’ preferences. For instance, any participants who experience problems with their username or forget their password, can email for a reminder or reset their password. An online tutorial is also available to demonstrate the features and functions of the intervention.

#### Control condition

The control condition is a mock-up focusing on severe mental illness accessed through the same trial website. It consists factsheets for siblings of people with mental illness which represent the best information available to them currently.

#### Intervention exposure

All participants across the four conditions will be asked to use the resources over the duration of the trial, i.e. over 10 weeks with a recommended usage of 1 to 2 hours per week. Weekly reminder via emails will be generated and sent to all participants to reinforce their use of the intervention. An online support centre is available to participants for queries over their usernames, passwords and/or any problems with access.

### Analysis

#### Quantitative data

Ordinal outcome data collected at baseline (T1), post-intervention (T2) and 10 week-follow up (T3) will be transferred into ranked scores, ready for analysis. Descriptive statistics focusing on variance and confidence interval estimation will then be performed. A variety of tests will be employed to compare within and between subjects, for example: Mann–Whitney and Wilcoxon Tests. Also ANOVA will be performed on ranked data. Following the framework and its elements for optimising trial parameters [27], the trial analysis will also provide data for calculating sample size and the effect size estimate for a future definitive trial. All analyses will be carried out using SPSS (SPSS, Inc.; Chicago, Illinois).

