**Figure 1 F1:**
[figure not shown]
Design of the study using MRC complex intervention framework, inclusive of time schedule for various phases.

The RCT comprises an exploratory trial, to complete the modelling and piloting phase of the MRC 4-phased framework [26]. The RCT employs a 2 by 2 factorial design, as illustrated by Figure 2. The factorial design gives the RCT 4 arms: 3 treatment conditions (covering: psychoeducation alone; peer support alone; and combined psychoeducation and peer support) and a control condition. This design is chosen to fit with the two active components in the intervention, i.e. psychoeducation and peer support. Considering that these two ingredients may work independently as well as inter-dependently, the three treatment arms allow an investigation not only to determine the effectiveness of the combined psychoeducation and peer-support treatment condition, but also of how each ingredient impacts independently on particular participants’ outcomes, minimising any contamination [26,27]. Hence, the factorial design RCT will aid our theoretical understanding of the intervention, how it works, how its ingredients interact with each other and ultimately how it supports changes in the targeted outcomes. Furthermore, the results using the factorial design will inform the optimal intervention to be used in the full scale trial.

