### Participants

#### Recruitment & Informed consent

Advertisement and recruitment will be conducted through a website developed and dedicated to delivery of the online information and peer support intervention produced by King’s College London; Early Intervention in Psychosis Services (EIPS); local carers groups and networks; and the Mental Health Research Networks (MHRN) across South-East England, including London. Care co-ordinators and clinicians working in EIPS in five NHS Trusts across South-East England will be given information about the trial in a series of presentation by the trial team. Clinicians will help identify potentially suitable participants from their case load of service users to the trial co-ordinator, with the service users’ and/or potential participants’ consent. The trial co-ordinator will make contact and provide further information about the trial to all potential participants. Individual consent from the participants will be sought following comprehensive information-giving and a consideration period of at least 3 days. Presentations will also be made at (family) carers and siblings events hosted by Rethink Mental Illness and other carers-related organisations/ networks over the period. Interested siblings may refer themselves directly to the research team to join the trial after the same information-giving, consideration and screening process.

Each of the five NHS Trusts covers a population of about one million and each has an EIPS caseload ranging from 400 to 600 service users at any one time. EIPS are dedicated mental health services for people aged between 16 to 35 who are affected by a first-episode psychosis [7]. The provision of service by EIPS usually starts from immediately following the onset of first episode psychosis, a critical period in determining long-time trajectory in recovery [5,7], and the treatment period is usually about three years. Following that, EIPS usually transfer the care of service users back to their GPs or to secondary mental health services for long-term support, e.g. community mental health teams. The time required to recruit 144 participants is estimated as 20 weeks. Contingency plans to address any short-fall in the recruitment include recruitment of additional participants to compensate for anticipated 20% attrition, extra time for recruitment and extension of the recruitment area to additional NHS Trusts within the geographical regions.

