#### Sample size

The exploratory trial is a feasibility pilot study to establish a preliminary estimate of the efficacy of an innovative intervention. The trial is not designed for hypothesis testing [24,25]. The pragmatic sample size of 120 participants for the trial was selected with reference to the general rule of thumb recommended by Lancaster et al. [27], taking account of the factorial design of this exploratory trial and the primary and secondary outcome measures to be investigated. A sample of 30 per arm is considered sufficient to obtain estimates of the values of outcomes for each arm and thus an estimate of the effect size which would then be used to inform the design of a definitive trial. To ensure the rule of thumb minimum sample of 30 will be retained in each arm, additional participants (i.e. N=144, n=36 in each arm) will be recruited to allow for an estimated attrition rate of up to 20%.

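### The methods named for the effect size use only siblings observed at each visit, though up to 20% attrition is expected; a repeated-measures mixed model on the same T1–T3 data would be better

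*Protocol article*

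**What the plan says.** **Attrition.** The Sample size section states that "additional participants (i.e. N=144, n=36 in each arm) will be recruited to allow for an estimated attrition rate of up to 20" per cent. The purpose is given just before: "To ensure the rule of thumb minimum sample of 30 will be retained in each arm". Thirty per arm is described there as enough to estimate outcomes and effect size. The recruitment section lists "recruitment of additional participants to compensate for anticipated 20% attrition" among its contingency plans. Extra recruits are the only response to attrition that the article states.

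**Visits.** All outcomes, including the primary outcome WEMWBS, are self-completed online at baseline (T1, week 0), "at end of intervention (T2=week 10) and at 10-week follow-up (T3=week 20").

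**Analysis.** Quantitative data plans ranked scores, descriptive statistics with confidence intervals, and then: "A variety of tests will be employed to compare within and between subjects, for example: Mann–Whitney and Wilcoxon Tests. Also ANOVA will be performed on" (scores converted to ranks). The same paragraph says that the trial analysis will supply the effect size and sample-size data for a definitive trial. SPSS is the named package.

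**Design.** "The RCT employs a 2 by 2 factorial design, as illustrated by Figure 2", with four arms of 36.

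**The concern.** Extra recruitment restores numbers. It does not restore the comparison between randomised groups if those who leave one arm differ from those who leave another. As named, Mann–Whitney at a visit uses only people with a score at that visit, the Wilcoxon test uses only complete pairs, and a conventional ANOVA uses only the records that enter it. A sibling with T1 and T2 but no T3 adds nothing to the T3 comparison, although the T1 and T2 scores say something about where T3 would have been.

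Selective loss is plausible here. The conditions differ in content and burden (modules with homework tasks, a moderated forum, both, or factsheets), and outcomes depend on people returning to a website. The Sample size section says that the trial is not designed for hypothesis testing, so the estimate is its main quantitative product and bias in it passes straight into the definitive trial.

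**Working it through.** **1. The plan's own figure.** 30 × 1.2 = 36 per arm and 120 × 1.2 = 144, as stated. At 20% loss, 36 × 0.8 = 28.8 per arm remain, and 57.6 on each side of a factorial margin. (36 keeps 30 only up to 1 − 30/36 = 16.7% loss; that is a separate point.)

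**2. Standard errors in SD units**, from √(2/n):
- arm v arm at T3: √(2/28.8) = 0.264
- factorial margin at T3: √(2/57.6) = 0.186
- arm v arm at T2, if half the losses come before T2: 36 × 0.9 = 32.4, √(2/32.4) = 0.248

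**3. Size of the shift.** The article gives no SD, no correlation between visits and no figure for how leavers differ, so all of these are assumptions: true effect zero, SD 1, correlation 0.6 between any two visits, half the losses before T2 and half before T3, drop-out depending on the last observed score with log-odds 1 per SD. Scenarios were simulated with 2 million people per group, and everyone observed at a visit was scored. Shifts are absolute, in SD.

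| Scenario | T2 | T3 | Change from T1 |
|---|---|---|---|
| (a) 20% loss in each group, selective in one only | 0.05 | 0.11 | 0.04 |
| (b) 20% loss in each group, selective in opposite directions | 0.11 | 0.22 | 0.07 |
| (c) 11% v 28% loss, low scorers leaving in both | 0.04 | 0.09 | 0.03 |
| (d) 20% loss in each group, same selection in both | 0.00 | 0.00 | 0.00 |

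**4. In standard errors**, smallest to largest of (a)–(c):
- T2, arm v arm: 0.04/0.248 = 0.16 to 0.11/0.248 = 0.44
- T3, arm v arm: 0.09/0.264 = 0.34 to 0.22/0.264 = 0.83, so about 0.35–0.85
- T3, factorial margin: 0.09/0.186 = 0.48 to 0.22/0.186 = 1.18, so about 0.5–1.2. This assumes that the pattern holds in both cells on each side of the margin.

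**5. What a likelihood model does.** In scenarios (a)–(c), with 1,000 simulated trials each at 36 v 36, a likelihood model on all observed T1, T2 and T3 scores had bias below 0.01 SD. With random loss its standard error was also lower, 0.20–0.21 against 0.26 SD, partly because it uses T1. A separate simulation (correlation 0.5, 7 of 36 lost per arm, selection in one arm) tested loss that depends on the unseen T3 score. There, using everyone's T1 and T2 cut the shift only from 0.15–0.29 to 0.10–0.21 SD.

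**6. Consequence, as illustration.** Suppose that the true effect is 0.40 SD (assumed). For 90% power at two-sided 5%, n per arm = 2 × (1.96 + 1.2816)²/δ² = 21.0/δ². At δ = 0.40 this is 132. With an upward shift of 0.10 it becomes 85, and with 0.20 it becomes 59. True power would then be 74% and 58%.

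**The case against.** **This is only an omitted missing-data section.** An article condenses the full protocol, and handling of missing data is commonly left to that document or the SAP, neither of which is shown. This stands as far as it goes: the absence of an imputation rule or analysis set is no finding. What can be criticised is the choice of methods the article does name, set beside the attrition it expects.

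**The list is open.** The tests are introduced as examples, could follow imputation, and are not expressly tied to the effect-size estimate. A reader might infer that the plan can score only those who stay, or that a sibling without T3 is discarded altogether. The text supports neither. Leavers are nowhere excluded, no repeated-measures ANOVA over T1–T3 is specified, and a sibling lost after T2 still counts in a T2 Mann–Whitney and a T1–T2 Wilcoxon test. What remains is that the methods, run as named, do not carry earlier scores into the later estimate.

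**The size can be overstated.** Restricting T2 to people who also completed T3 gives shifts of 0.15, 0.30 and 0.13 SD in scenarios (a)–(c), but the T2 tests as named impose no such restriction. Under these assumptions no arm contrast shifts by more than one standard error. A factorial margin does so only at T3 with opposite selection.

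**Selective drop-out is not shown.** A reader might infer from the Process evaluation section that it is the expected case. That passage explains purposive selection for interviews and says that experiences may affect usage and outcomes; it does not address drop-out. All arms also have the same site, recommended usage and weekly reminders. Differential loss is plausible, no more, and equal selection gives no bias.

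**Within-subject comparisons are planned.** These are less affected, as the change-from-T1 column shows, but the shift does not vanish when selection differs.

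**Conclusion.** The point holds as one about choice of method. The article expects a loss of up to one fifth, rests its estimate on those retained, and names methods that leave leavers' earlier scores out of the later comparison, when the data for a better analysis are already planned.

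The size is conditional. It needs drop-out that differs by arm and depends on earlier wellbeing, at the assumed strength, and the article supplies neither. On those assumptions the effect on the T3 estimate ranges from modest to, in one factorial case, slightly more than one standard error. At T2, and for change from T1, it is small. The case for the change rests as much on its low cost and the gain in precision as on the bias.

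**What to change.** In Analysis – Quantitative data, take the effect size for the definitive trial from a linear mixed model for repeated measures on the WEMWBS score. Include all randomised participants in their allocated arm, all observed T1, T2 and T3 values, and arm-by-visit terms written as the two factors and their interaction, each by visit. Keep the Mann–Whitney, Wilcoxon and rank ANOVA results as description.

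Report loss by arm and visit, with leavers' baseline scores. Add one sensitivity analysis that shifts leavers' unobserved scores in the active arms, for example by 0.25 and 0.5 SD.

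**Cost.** Analysis wording only: no extra participants, visits or data, and SPSS fits the model. The downside is small. The model treats WEMWBS, a 14-item scale with five response categories, as continuous, and assumes that loss is explained by observed scores. It does not remove bias from drop-out that depends on unobserved scores, which is why the sensitivity analysis is needed.
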